### Safety assessment

3.3

From baseline to the end of the study, physical examinations will be performed daily. Routine blood and urine tests, routine stool tests with occult blood, liver and renal function tests, and electrocardiograms will be performed at baseline, on day 7 and 14, and any adverse events during the study period will be observed and recorded in detail.

### Compliance

3.4

Once the patients are randomly divided into groups, the researchers will pay close attention to the patients’ vital signs. In the case of any drug-related adverse events or other disease conditions, the physical condition of the patients will be evaluated immediately to determine whether they can continue to participate in the study and effective interventions will take place for any adverse events.

### Adverse events

3.5

Regardless of its relationship with the study intervention, any adverse event will be recorded in the CRF. If any serious adverse event occurs, the intervention will be stopped immediately and details concerning the time, severity, relationship to the drug, and corresponding measures will be taken according to the standard operating procedures of the Chinese Food and Drug Administration. In addition, serious adverse events will be reported to the steering committee and ethics committee within 24 hours.

### Data management and quality control

3.6

All records will be collected in the CRF and will be completed by trained and qualified investigators. After the CRF is completed, if corrections are made, the original record will not be altered, and the clinical examiner will review the completed CRF. Data input and management will be conducted under the guidance of medical statistics experts. To ensure the accuracy of the data, 2 data administrators will input and proofread the data. After checking and confirming that the established database is correct, the data will be locked by the main researchers and statistical analysts. Locked data or files will not be changed at a later date and will be submitted to the study groups for statistical analysis. The Sichuan Evidence-Based Medicine Center of TCM (Chengdu, China) has no competitive interest and will be responsible for monitoring the data. The scientific research office of the Chengdu University of TCM, which is independent of the researchers, will conduct a data review during the study.

### Statistical analyses

3.7

Before analysis, 2 similar participants with complete data will be carefully examined to ensure that the data is correct. All data analyses will then be based on treatment intention.

The data will be analyzed using the statistical software package SPSS 22.0 (Chicago, IL). The analysis method will be selected according to the distribution characteristics of the data. The measured data will be expressed as the mean ± the standard deviation. First, the normal test and the homogeneity test of variance will be performed. In the case of normal distribution and equal variance, a *t*-test will be performed; otherwise, a nonparametric test will be utilized. The difference will be statistically significant when *P* ≤ .05.

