### Sample size

2.4

Calculating the sample size was based on the effective rate. According to previous research, the effective rate for the treatment group with integrated traditional Chinese and Western medicine is 65.2%, and effective rate for the group with Western medicine alone is 34.8%. The software Power Analysis and Sample Size version 11.0 (PASS 11.0)was used to calculate the sample size of the 2 groups, assuming that 10% of patients are likely to be lost during follow-up, a total of 110 patients will be enrolled.

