**Table 3 T3:**
[figure not shown]
Quantitative standard for the classification of symptoms and signs.

The criteria for determining the therapeutic effect of TCM will be formulated in accordance with the guiding principles for clinical research for new TCM drugs^[25]^ (Trial) and the criteria for the therapeutic effect of the diagnosis of diseases and syndromes of TCM issued by the Chinese Society of TCM.

(1)Cure: the clinical symptoms and signs disappear or basically disappear, and the laboratory examination reveals visible improvement. The TCM syndrome score is reduced by more than 95%.(2)Significant effect: the clinical symptoms, signs, and laboratory tests are significantly improved. The TCM syndrome score is reduced by ≥70%.(3)Effective: the clinical symptoms, signs, and laboratory tests are improved. The TCM symptom score is reduced by ≥30%.(4)Invalid: the clinical symptoms and signs are not improved or have worsened. There is a < 30% reduction in the TCM symptom score.

2. PɑO2/FiO2: before and after the intervention, we will perform arterial blood gas analyses to measure changes in the PɑO2/FiO2.

3. Extravascular pulmonary water index: will be obtained from the PiCCO monitor (It is a tool to detect the main hemodynamic parameters of severe patients)

4. Length of time with ventilator: the time with the ventilator will be 14 days from the patient participating in the trial to the treatment.

5. ICU length of stay: the actual length of stay = date of leaving the ICU - date of entering the ICU + 1.

6. 28-day mortality: the mortality rate from the beginning of the trial to the 28th day will be recorded.

7. Follow-up records: During the follow-up period, the all-cause mortality, respiratory failure mortality, and readmission rate in the 1-year period after discharge will be recorded. Criteria for readmission: subjects readmitted for ARDS or other respiratory diseases, not including any other disease or reason. If readmission occurs during the follow-up period, the readmission rate will not be recorded during the follow-up period. Readmission rate = number of patients readmitted/number of patients who completed follow-up.

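### Tests on the trial data choose between an unadjusted t-test and a rank test for measured outcomes, so the question tested depends on the pre-test and baseline precision is lost

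*Protocol article*

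**What the plan says.** Statistical analyses (3.7) is the only analysis rule in the article. It opens with the principle that "The analysis method will be selected according to the distribution characteristics of the data", then fixes the order of steps: "First, the normal test and the homogeneity test of variance will be performed". If the data pass both, a t-test is used; "otherwise, a nonparametric test will be utilized". The nonparametric test is not named. The summary does not change with the test: "The measured data will be expressed as the mean ± the standard deviation". The threshold is P ≤ .05. No covariate is named.

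Determination of results (3.2) shows that two outcomes have a before-treatment value. For PaO2/FiO2, "before and after the intervention, we will perform arterial blood gas analyses to measure changes in the" ratio. The TCM syndrome score is recorded before and after treatment, and the percentage reduction defines the response categories. For the extravascular lung water index, the text states no baseline measurement.

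**The concern.** Three features of the written rule work against each other.

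- **The test is chosen from the outcome data.** Two runs of the same trial could test different hypotheses on the same outcome, depending on two preliminary tests.
- **Unequal variance alone triggers the rank test.** A rank test asks whether a patient in one arm tends to have a higher value than a patient in the other. When spreads differ, that is not the question of equal means, yet means and SDs are what will be shown. The P value and the summary can then describe different quantities.
- **Neither test adjusts for baseline.** The before values exist for PaO2/FiO2 and the TCM score, and with about 50 patients per arm the unused precision matters.

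At stake are a P value for a mean difference that may not be about the mean difference, and wider intervals than the data need.

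**Working it through.** **Inputs from the article.** 110 patients, 1:1, 10% loss (Design; Sample size): 110 × 0.90 = 99, or 49.5 per arm, taken as 50. Threshold P ≤ .05, read as two-sided because sidedness is not stated. The rule itself carries no figure to reproduce.

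**Assumptions, because the article gives none.** Shapiro-Wilk in each arm and Levene's test, both at 5%; Mann-Whitney as the nonparametric test; the means, SDs, distributions and baseline correlations below.

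**Step 1. Rejection rates of the rule when the two means are equal** (4,000 simulated trials per row; a range shows repeated runs):

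| Data, 50 per arm | Rule rejects | Welch rejects |
|---|---|---|
| Lognormal, mean 200, SD 60 vs 120 | 23–24% | 5–6% |
| Lognormal, mean 200, SD 80 vs 120 | 12–13% | 5–6% |
| Normal, SD 40 vs 80 | 5.7–6.4% | 5.0–5.6% |
| Normal, SD ratio 1:3 | 6.7% | 4.4% |
| Normal, equal SD | 4.5–5.4% | 4.5–5.1% |
| Lognormal, identical arms (SD 60, 80 or 120) | 4.8–5.9% | 4.7–5.7% |

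In the two unequal lognormal rows the rank test was chosen in more than 99% of trials. In the normal, equal-SD row, where nothing is wrong with the data, the pre-test still sent about 14% of trials to the rank test.

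**Step 2. Why the skewed rows move.** For a lognormal with mean m and SD s, the log-variance is v = ln(1 + s²/m²) and the median is m / √(1 + s²/m²).

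- SD 60: v = ln(1.09) = 0.086, median 200/√1.09 = 191.6.
- SD 80: v = ln(1.16) = 0.148, median 200/√1.16 = 185.7.
- SD 120: v = ln(1.36) = 0.307, median 200/√1.36 = 171.5.

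The chance that a value from the narrower arm exceeds one from the wider arm is Φ[((v₂ − v₁)/2) / √(v₁ + v₂)]:

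- SD 60 vs 120: Φ(0.111/0.627) = 0.57.
- SD 80 vs 120: Φ(0.080/0.675) = 0.55.

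The rank test detects this departure from 0.50 although the means are the same. It answers its own question properly, but not the one that the reported means pose.

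**Step 3. Precision left unused.** With equal variances before and after and correlation r, in units of the post-treatment variance, the residual variance is 1 for post-treatment values, 2(1 − r) for changes and 1 − r² for ANCOVA.

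| r (assumed) | Change score | ANCOVA | Saving vs post value | Saving vs change |
|---|---|---|---|---|
| 0.3 | 1.40 | 0.91 | 9% | 35% |
| 0.4 | 1.20 | 0.84 | 16% | 30% |
| 0.5 | 1.00 | 0.75 | 25% | 25% |
| 0.6 | 0.80 | 0.64 | 36% | 20% |

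As an illustration, power = Φ(d/√(2·variance/50) − 1.96). For an assumed effect of d = 0.5 SD and r = 0.5, this gives 70.5% for either unadjusted comparison and 82.3% for ANCOVA.

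**The case against.** **The error rate is mostly sound.** A reader might infer from the 24% and 12% that the rule does not hold 5% in general. The article does not support that. Those rows need skewed data with equal means and unequal spread, and the article reports no SD or distribution. In them the medians also differ, so treatment has changed the distribution. If treatment does nothing to any patient, the arms share one distribution and the rule stays near 5–6%. This objection stands and limits the claim.

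**Baseline is not ignored.** The percentage score reduction and the change in PaO2/FiO2 both use the before value, and an unadjusted comparison is valid in a randomised trial. This also stands. What is absent is adjustment, so this part concerns efficiency, not bias.

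**Proportions.** A reader might add that a t-test or rank test does not suit the efficacy rate, although "Calculating the sample size was based on the effective rate", nor mortality or readmission. The rule is worded for measured data; on rates the text is silent, and their method may sit in a fuller document that is not shown. That is no fault here.

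**Detail may be in the analysis plan.** That would answer an omission. It does not answer a rule that the article writes out and nowhere corrects.

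**Deaths before the second measurement.** ANCOVA does not settle how these patients are counted. That is true, but the present rule does not settle it either; it is a separate question.

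**Conclusion.** The concern holds for the measured outcomes. The rule lets the data choose the hypothesis, sends unequal variance to a rank test while means and SDs are reported, and leaves baseline out of the comparison. The main harms are a test question that depends on the pre-test and lost precision: 9–36% of the variance against post-treatment values, or 35–20% against changes, if the baseline correlation lies between 0.3 and 0.6. A false signal on the mean difference is a conditional risk. It is large in the assumed skewed, unequal-spread cases and small otherwise. The sample size of 110 and the binary efficacy rate behind it are unaffected. The change should be made, but the trial does not fail without it.

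**What to change.** In Statistical analyses, delete the normality and variance tests as a means of choosing the analysis, and name the method for each measured outcome in advance.

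- **PaO2/FiO2 and the TCM score as a measured quantity:** ANCOVA of the post-treatment value on arm, baseline value and centre, with robust standard errors, reporting the adjusted difference with its 95% CI.
- **Extravascular lung water index:** the same, if a baseline value is recorded.
- **Means compared without a baseline value:** Welch's test.

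The cost is a change of wording, made before the database is locked. For PaO2/FiO2 and the TCM score it uses values already due to be collected. It needs no extra patients or visits, and it runs in the software that the article names.

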### Ethics and communication

3.8

The clinical trial has been reviewed and approved by the Sichuan Regional Ethics Review Committee of TCM/The Medical Ethics Committee of the Affiliated Hospital of Chengdu University of TCM (No. 2018-kl070). In order to protect the privacy of the subjects, only participating supervisors and researchers will have access to the patients’ medical records, and they will keep all patient information confidential. The ethics committee and the drug administration have the right to examine the record of clinical trials. All treatment results will be fully preserved and available to the patient and family members. The patient's research status during the follow-up period will be requested using phone interviews.

## Discussion

4

ARDS is a major public health concern that seriously affects the quality of life and endangers the life of patients. At present, there is no specific treatment for ARDS; management primarily relies on supportive care. The economic burden of ARDS is a pressing concern worldwide.^[26,27]^ Therefore, finding effective treatment methods to improve prospects is urgent. At present, a large sample study to determine the efficacy and safety of JWQYD for the treatment of ARDS is lacking, so we will conduct a prospective randomized controlled trial to determine the risks and benefits of JWQYD in the treatment of ARDS.

This study has the following advantages: from the perspective of evidence-based medicine, this study is designed as a randomized, double-blind, placebo-controlled trial, which is considered the most authoritative research method. At the same time, this is a multicenter study conducted in 4 comprehensive Grade-A hospitals in China, which improves the external effectiveness and representativeness of the sample and reduces the risk of selection bias. Additionally, to ensure quality, all staff in the study will be required to complete a SOP (Standard Operation Procedure) training of the study procedure beforehand. Since the main stage of the study will be carried out during hospitalization, the staff will be able to quickly identify and manage adverse reactions to ensure the safety of the subjects. After discharge, researchers will maintain good telephone communication with patients and their families. However, there are some limitations to the design of the study, such as the failure to ensure that a 14-day treatment period will be the ideal length.

In summary, the purpose of this study is to determine whether JWQYD can be used as an adjuvant therapy with Western medicine in the treatment of ARDS patients, and to potentially provide objective evidence of its effectiveness and safety. If the hypothesis is confirmed, that is to say, the comprehensive plan of integrated traditional Chinese and Western medicine is relatively safe and more effective than treatment with Western medicine alone, then it can be recommended that patients with ARDS be treated with the qianyang pill to improve their clinical course.
